#### Study participants and enrollment period

Women accessing health care for HIV care and treatment services at CHC, between the ages of 25–49 years of age will be approached for enrollment into the study and subsequent cervical cancer screening. Following the “Model” Participant period, enrollment of participants will continue for a total of 30 months (Table 2).

**Table 2 Tab2:** Inclusion and Exclusion criteria

Inclusion Criteria	Exclusion Criteria
Women 25–49 years, accessing HIV care and treatment services	Physical or mental impairment that inhibits participation in the study
Not being pregnant	Pregnant women or < 6 weeks post-partum
Patients with a cervix (women who have undergone a total hysterectomy with removal of the cervix are not eligible)	

#### Study procedures and the cervical cancer *Screen-Triage-Treat *care cascade

After providing informed consent, the study clinician will open a Case Report Form (CRF) for each patient which starts with a brief questionnaire which will include the participant’s demographic information and medical history, including HIV viral load and CD4 counts, previous cervical cancer screening results if previously screened, and result of rapid pregnancy test performed that day. Each participant will then be accompanied to a private location where the study clinician will provide counseling and instruction on how to appropriately perform the self-collection vaginal swab technique. Data on HPV testing, VIA results, and referrals along each step of the process will be documented in the CRF.

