### Aims/objectives

The overall aim of this study is to evaluate implementation best practices for deploying a *Screen-Triage-Treat* approach to cervical cancer screening utilizing self-collected HPV DNA testing among HIV-infected women in care within select health facilities in Chókwè District, Mozambique. The main objectives of this study are:To develop an in-depth understanding of the HPV *Screen-Triage-Treat* care cascade within the HIV care and treatment services based on a collaborative, exploration-focused process with local stakeholders.To evaluate the effectiveness of the *Screen-Triage-Treat* approach to cervical cancer screening utilizing self-collected HPV DNA testing.To use the Consolidated Framework for Implementation Research (CFIR) to identify factors that explain site-level and provider-level variation in the implementation of the *Screen-Triage-Treat* approach to cervical cancer screening utilizing self-collected HPV DNA testing.

Table 1 shows the SPIRIT diagram including the schedule of enrollment, intervention, and assessment.

**Table 1 Tab1:** SPIRIT diagram: schedule of enrollment, intervention, and assessment

Study Period	Pre-Implementation Phase	Implementation Phase	Follow-up Phase	Post-implementation Evaluation
Timepoint	Month −2 to 0	Month 0–30	Month 1–30	Month 31–33
Enrollment:				
Site preparation and staff training	X			
Two-week pilot assessment period	X			
Model participant enrollment (1–2/day)		X		
Participant eligibility screening		X		
Informed Consent		X		
Intervention:				
Self-collected HPV DNA testing (Screen)		X		
HPV result reporting (same-day CHC; weekly in periphery)		X		
VIA and thermal ablation if eligible (Triage-and-treat)		X		
Referral to higher level of care for LEEP/colposcopy in not eligible for ablation		X		
Assessments:				
Baseline retrospective data (past 12 months)	X			
Process mapping/group model building workshop and qualitative interviews (Objective 1a-c)	X	X		
Quantitative data collection (HPV, VIA, treatment rates)		X		
Implementation Outcomes (adoption, fidelity, reach, acceptability)		X	X	
Qualitative provider interviews (CFIR domain)			X	
Statistical analysis of primary outcome (proportion of HPV + women treated, Objective 2)			X	
Analysis of secondary outcomes (implementation outcomes, Objective 3)			X	
Dissemination workshops and final reporting				X

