#### Model participant period

At the conclusion of the two-week assessment period, we will begin enrollment of “model” participants. During this time, participants will be enrolled, contribute data, and complete longitudinal follow-up, but enrollment will still be limited to 1–2 participants per day. Data will be presented to the study PIs daily, documenting the number of women accepting self-screening; the number of women who were HPV screen positive; and the number of eligible women who received thermal ablation on the same day (or were referred for higher level care if needed). Once the site has enrolled a minimum of 20 participants (5 each at each of the peripheral health facilities) and the study staff feel comfortable with the enrollment procedures, the site will go live.

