#### Visual Assessment for Treatment (VAT)

Women with a positive HPV test will undergo visual assessment for treatment (VAT) followed by ablation using thermal ablation, if eligible (Fig. 3). Women with lesions not eligible for ablation will be referred to the neighboring Hospital Rural of Chókwè for LEEP or other treatment, as appropriate. During the examination, the health care provider will also use a smart phone device to take images/videos of the cervix so that he or she will be able to document the test results and perform quality control. Participants will be asked if they agree with having their images/videos used for future research. If they agree, a future use research informed consent document for the photo will be reviewed and signed. Images/videos collected to be used for future research will be de-identified.

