#### Date collection

Prior to intervention roll-out, baseline data will be retrospectively collected for the prior 12 months at each of the selected study sites, including the number of women accessing care for HIV care and treatment services each month; the number of women screened for cervical cancer through standard of care protocols; the proportion of screen-positive women who then received treatment or referral for treatment, and the length of time between screening positive and receiving treatment, if appropriate. Data will be collected by study team members (physician, nurse, or medical technicians) utilizing a paper-based instrument and then uploaded into a password-protected, tablet-based, online research data capture (REDCap) database. This method allows for the recording of demographic information, medical and medication history, and any pertinent laboratory test results. Data quality control will be conducted by study investigators who will review all completed paper-based study instruments and confirm the accuracy of data entered into REDCap.

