#### Outcome measures

Our primary outcome measure is the number of women screened and the proportion of screen-positive women successfully undergoing treatment. Secondary outcomes measures will include other implementation outcomes (see Specific Objective 3 below), and if successful, will be utilized to inform future research to take this approach to scale across Mozambique.

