#### Sample size and power calculations

We used our primary outcome, more specifically, the proportion of HPV screen positive women that will successfully undergo treatment, to power the study. We used preliminary data to estimate a sample size sufficient to detect, with 90% power, an improvement of at least 15% in the proportion of women undergoing treatment compared to the current standard of practice. CHC currently sees approximately 1,200 HIV adult outpatient visits per month, of which 52% are female (*n* = 624) and approximately 75% of women are between the ages of 25–49 years (*n* = 468). Of these, we conservatively expect approximately 60% will not have been screened in the last three years and meet screening eligibility (*n* = 280). Based on preliminary data, the prevalence of HPV-positivity among WLWH was estimated to be approximately 40%; however, in our calculations, we again took a more conservative approach and assumed an HPV prevalence of 35% (*n* = 98). Under the current standard of care scenario we estimate that approximately 36% of HPV screen positive women go on to receive treatment (CHC currently performs, on average, 35 thermal ablation procedures per month). Figure 4 below shows statistical power curves to detect improvements, through utilization of the HPV self-testing *Screen-Triage-Treat* approach, varying from 10 to 20% in the proportion of HPV-screen positive women undergoing same day thermal ablation, compared to standard of care. We used a type-I error fixed at 5%, two-sample, two-sided binomial test, and assumed trimestral cumulative data to plot the curves, for different prevalences of HPV. Calculations were performed using the R software (*pwr* R package) [28]. Based on Fig. 4, we will be able to detect over 15% improvements in the proportion of HPV-screen positive women undergoing same day thermal ablation compared to standard of care, while assuming a prevalence of 35% or even lower at 25%, with at least 90% power.

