#### Statistical analysis plan

Using data captured during implementation of the *Screen-Triage-Treat* approach for cervical cancer screening, we will evaluate intervention fidelity as a function of 1) *Completion Rate*: the proportion of enrolled women who turned in a self-collected sample for HPV DNA testing; 2) *Test Result Notification Rate*: the proportion of women who were notified of their HPV DNA test result on the same day as sample collection; and 3) *Treatment Rate*: the proportion of screen-positive women who were treated with thermal ablation, if appropriate, or referral for higher level of care.

Patients’ characteristics and clinical values will be summarized in tables and figures. Continuous variables will be presented as medians and interquartile ranges. Categorical variables as frequencies and percentages. Descriptive statistics will be done for the overall population and stratified intervention status and study site. Continuous variables will be compared via the Mann–Whitney-Wilcoxon test, and categorical variables will be compared via the chi-square test. We will use a generalized linear model (GLM) with the logit link to and perform an interrupted time series to assess the impact of the intervention and the proportion of patients who subsequently underwent treatment for cervical cancer. The model will regress the outcome on intervention status (binary variables, yes/no), calendar time (in months), and an interaction between the two terms. By doing this we will be able to assess the immediate impact of the intervention (also known as level change) as well as its effect over time (sustained effect of the intervention) compared to the counterfactual scenario of no intervention being implemented. Analysis and comparisons will be performed overall, combining all sites, as well as being stratified by health facilities. We will adjust for relevant demographic and clinical characteristics, such as age, CD4 count, and viral load, among other factors. Continuous variables will be modeled via restricted cubic splines. We will again use GLM with a gaussian link to estimate the impact of the intervention on the number of WLWH diagnosed with HPV, adjusting for the same covariates as above, and following the same steps as above (e.g., another interrupted time series). If the normality assumption is violated, we plan to use ordinal regression models as an alternative. We do not expect issues with statistical over-fitting.

### Specific objective 3

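### The primary outcome is treatment received, but for women not eligible for ablation the named data stop at referral, and two of the plan's measures count referral as success

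*Protocol article*

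**What the plan says.** The Outcome measures section makes treatment received the endpoint: "Our primary outcome measure is the number of women screened and the proportion of screen-positive women successfully undergoing treatment". Four other places in the protocol article handle women not eligible for ablation differently.

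- **Case report form** (Study procedures and the cervical cancer Screen-Triage-Treat care cascade): "Data on HPV testing, VIA results, and referrals along each step of the process will be documented in the CRF". The daily data described under Model participant period likewise cover same-day ablation or referral.
- **Baseline** (Date collection): "the proportion of screen-positive women who then received treatment or referral for treatment".
- **Treatment Rate** (Statistical analysis plan): "the proportion of screen-positive women who were treated with thermal ablation, if appropriate, or referral for higher level of care".
- **Power** (Sample size and power calculations): the curves are for improvements "in the proportion of HPV-screen positive women undergoing same day thermal ablation, compared to standard of care".

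On where treatment happens, the Visual Assessment for Treatment (VAT) section says: "Women with lesions not eligible for ablation will be referred to the neighboring Hospital Rural of Chókwè for LEEP or other treatment, as appropriate". Onward referral may be to Xai-Xai Provincial Hospital or Maputo Central Hospital. None of these is among the four facilities listed under Study setting. Table 1 has an intervention row, "Referral to higher level of care for LEEP/colposcopy in not eligible for ablation", but no separate row for the result of that referral.

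**The concern.** A referral is a step towards treatment, not treatment. The named data show that a woman was sent on. They do not show whether she attended or had a procedure, and no section describes how that information returns from the referral hospital.

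The gap affects the endpoint because the plan's own measures fill it in different ways. The Treatment Rate and the baseline measure score a referral as success. The same-day ablation measure scores a completed LEEP as a non-event. Neither gives the proportion of women who were treated. If the combined measure is carried into the primary analysis, the study could report a higher treated proportion without any further woman confirmed as treated, and it could not detect loss between referral and procedure.

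**Working it through.** **1. The plan's own figures.** Inputs are from Sample size and power calculations.

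- Volume: 280 × 30 = 8,400 screened; 8,400 × 0.35 = 2,940 screen-positive; 2,940 × 0.15 = 441 added treated women. All three reproduce.
- Power: 98 screen-positive women per month × 3 = 294 per group, 36% against 51%, two-sided 5%. The formula is z = [|p2 − p1|√n − 1.96√(2p̄(1 − p̄))] / √[p1(1 − p1) + p2(1 − p2)], with p̄ = 0.435. This gives (2.572 − 1.374) / 0.693 = 1.73, or 95.8% power. The arcsine method of the pwr package also gives 95.8%. The statement of at least 90% at 35% prevalence holds for a 15-point difference.
- Control rate: 35 ablations per month / 98 = 35.7%, stated as 36%. It therefore appears to be a rate of ablation only.

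The arithmetic is sound. The question is which event it counts.

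**2. How a woman referred for LEEP is scored.**

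| Section | Referred, procedure done | Referred, no procedure |
|---|---|---|
| Outcome measures (treated) | success | failure |
| Date collection, baseline (treated or referred) | success | success |
| Statistical analysis plan, Treatment Rate (ablated or referred) | success | success |
| Sample size, power curves (same-day ablation) | failure | failure |

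Only the first row separates the two kinds of woman, and it is the one for which no data source is described.

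**3. Effect on the implementation-period proportion.** Let x be the share of HPV-positive women referred. The article does not give it, so 10–25% is an assumption.

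- Women concerned: 0.10 × 2,940 = 294; 0.25 × 2,940 = 735.
- For illustration, let 51% of ablation-eligible women be ablated. The overall proportion is 0.51(1 − x) if no referred woman counts and 0.51(1 − x) + x if all count:
  - x = 10%: 45.9% against 55.9%
  - x = 20%: 40.8% against 60.8%
  - x = 25%: 38.25% against 63.25%
- The gap always equals x.

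**4. Effect on the before-after contrast.** Let a be the share ablated, x the share referred and c the share of referred women whose treatment is completed, with 0 for baseline and 1 for implementation.

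- Referral counted as success: (a1 + x1) − (a0 + x0).
- Treatment received: (a1 + c1x1) − (a0 + c0x0).
- Error in the contrast: x1(1 − c1) − x0(1 − c0).

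The error is zero only if unconverted referrals form the same share in both periods. The plan gives no reason to expect this, since baseline screen-positives come from standard-of-care screening and not from HPV testing.

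A worked case: hold ablation at 36% and let x1 be 15% (assumed). Counting referrals gives 36 + 15 = 51%, the whole planned effect against the planning rate, with no further woman confirmed treated. If the baseline is also scored as treated or referred and x0 is 15%, both periods read 51% and the contrast is zero.

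**5. Timing.** In Table 1 the Implementation Phase and the Follow-up Phase both end at Month 30, and the primary analysis sits in the Follow-up Phase. A woman referred near Month 30 has little or no scheduled time in which a completed procedure could be seen.

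**The case against.** The strongest reply is that this is a journal article. Case report form pages and register abstraction are usually left to the full protocol, and the article does point to more than referral. Table 1 schedules collection of treatment rates over Months 0–30. Model participants "participants will be enrolled, contribute data, and complete longitudinal follow-up". The case report form sentence is plainly not exhaustive, because it omits thermal ablation, which the Model participant period section shows is recorded.

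This stands against a stronger reading. A reader might infer that no assessment of treatment is scheduled, or that the outcome is unmeasured for every woman not eligible for ablation. The article does not support either. The treatment-rates row is not limited to ablation, the content of follow-up is simply not described, and under the combined and same-day measures these women do have a value. A form not shown may hold a field for completed LEEP.

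Three further limits also stand. The loss to follow-up described in the Background concerns women positive on visual inspection who were not ablated at the same visit, so it is not evidence of loss after referral. Nothing shows that referred women have the worst lesions, because ineligibility can also be anatomical. Nor can a 10–25 point error in the estimated effect be claimed: x is assumed, and the shift is in one period's proportion.

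The reply does not remove the conflict in what the article states. The baseline measure and the Treatment Rate are explicit, and both put referral in the numerator. The treatment-rates row does not settle the matter, because the only Treatment Rate the article defines is that one.

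**Conclusion.** The point holds as a conflict between the endpoint and the data and measures given for it. The primary outcome is treatment received; the baseline and the Treatment Rate accept referral in its place; the power statement uses same-day ablation; and no route is described by which treatment completed at a referral hospital reaches the study. Applied as stated, the combined measures score an unconfirmed referral as treatment and cannot show loss after referral.

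The size is x for the implementation-period proportion: 10–25 points, or 294–735 of 2,940 women, if 10–25% are referred. That range is an assumption. The error in the before-after contrast is x1(1 − c1) − x0(1 − c0) and cannot be computed from the article. Confidence is moderate, because the full protocol or the case report form may already collect completion.

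**What to change.** 1. **One numerator.** In Outcome measures, Date collection, Sample size and power calculations, and Statistical analysis plan, define the primary event as confirmed treatment: ablation at the study site, or a procedure confirmed at the referral hospital within a fixed window, for example 90 days. Report referral as a separate cascade step.
2. **A data source.** Add a referral-outcome item (attendance, procedure, date) to the case report form and to Table 1. Existing staff would fill it from the Hospital Rural registers, and from Xai-Xai or Maputo where a woman was referred onward. If the full protocol already has such an item, cite it.
3. **Timing.** Let the window run past Month 30 for women referred late, and place the primary analysis after it closes.
4. **Baseline.** Collect treatment and referral as separate items for the prior 12 months. Apply the same confirmation as far as the registers allow, linking on facility identifiers, since the article gives these women no study ID.
5. **Sensitivity analysis.** Score unconfirmed referrals as all treated and as none treated. This brackets the understatement that comes from counting only confirmed procedures.

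The cost is abstraction of about 10–25 records a month under the assumed share (294 / 30 = 9.8; 735 / 30 = 24.5), a data-access permission, and a later primary analysis. The treated proportion will probably look less favourable. Clinical care does not change.

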#### Laboratory procedures at CHC

Directly following collection of the vaginal swab sample, the participant will be taken back to the waiting area and her sample will be taken to the laboratory for HPV testing using the Xpert HPV Test on the GeneXpert platform (Cepheid, Sunnyvale, CA, USA). This point-of-care test takes approximately one hour to get results. Participants will be asked if they agree with having any remaining sample volume after HPV testing used for future research. If they agree, a future use research informed consent document will be reviewed and signed.

#### Laboratory procedures at CS da Cidade, CS Urbano, and CS de Chalucuane

Directly following collection of the vaginal self-swab sample, the sample will be placed into a vial with PreserveCyt (ThinPrep System, Hologic Inc, Marlborough, Massachusetts, USA). At a minimum of once per week, samples will be transported to CHC and subsequently tested using the XPert HPV test as described above. Participants will be asked if they agree with having any remaining sample volume after HPV testing used for future research. If they agree, a future use research informed consent document will be reviewed and signed. Results will be picked up the following week when new samples are brought into CHC and distributed to each health facility.

#### Visual Assessment for Treatment (VAT)

Women with a positive HPV test will undergo visual assessment for treatment (VAT) followed by ablation using thermal ablation, if eligible (Fig. 3). Women with lesions not eligible for ablation will be referred to the neighboring Hospital Rural of Chókwè for LEEP or other treatment, as appropriate. During the examination, the health care provider will also use a smart phone device to take images/videos of the cervix so that he or she will be able to document the test results and perform quality control. Participants will be asked if they agree with having their images/videos used for future research. If they agree, a future use research informed consent document for the photo will be reviewed and signed. Images/videos collected to be used for future research will be de-identified.

**Fig. 3 Fig3:**
[figure not shown]
Flow diagram for HPV DNA testing in Women Living with HIV. *HPV = Human papillomavirus; VIA = Visual Inspection with Acetic Acid; TA = Thermal ablation; and LEEP = Loop Electrosurgical Excision Procedure

Following assessment as described above, women who screen positive will be eligible for ablative therapy if there is no suspicion of invasive or glandular disease, and if:The transformation zone (TZ) is fully visible, the whole lesion is visible, and it does not extend into the endocervix; orThe lesion is type 1 TZ (when it only contains ectocervical components); orThe lesion is type 2 TZ where the probe tip will achieve complete ablation of the squamocolumnar junction (SCJ) epithelium, i.e., where it can reach the upper limit of the TZ. Sometimes the SCJ can be seen high in the canal, but a probe tip would not reach it.

Women are not eligible for ablative therapy if there is any suspicion of invasive or glandular disease (i.e., adenocarcinoma or adenocarcinoma in situ), and:The TZ is not fully visible because it is endocervical (Type 3 TZ), orIt is a type 2 TZ where the SCJ is out of reach of the probe tip.The lesion(s) cover > 75% of the cervix.

If the above criteria for ablation are not met, the woman will be referred to a gynecologist at the closest facility (Hospital Rural of Chókwè). The clinician will evaluate the patient with colposcopy, cervical biopsy, endocervical curettage, and/or immediate LEEP as appropriate per standard guidelines. Women diagnosed with invasive cervical cancer or requiring further diagnostic workup not feasible in this facility will be referred to either Xai-Xai Provincial Hospital (HPX) or Maputo Central Hospital (HCM).

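### The eligible and not-eligible lists for ablation are not complements, so for two groups of women without suspected cancer the choice between ablation and referral depends on how the text is read

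*Protocol article*

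**What the plan says.** All of this stands in the protocol article under Visual Assessment for Treatment (VAT), mostly below the caption of Fig. 3.

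- **Entry to the step.** "Women with a positive HPV test will undergo visual assessment for treatment (VAT) followed by ablation using thermal ablation, if eligible".
- **Eligible list.** A screen-positive woman is "eligible for ablative therapy if there is no suspicion of invasive or glandular disease, and if:The transformation zone (TZ) is fully visible", with the whole lesion visible and not reaching the endocervix; *or* she has a type 1 TZ; *or* she has a type 2 TZ that the probe tip can ablate completely. The text adds that the SCJ can sometimes be seen high in the canal but not reached by the probe.
- **Not-eligible list.** It opens "Women are not eligible for ablative therapy if there is any suspicion of invasive or glandular disease (i.e., adenocarcinoma or adenocarcinoma in situ), and". Its items are "The TZ is not fully visible because it is endocervical (Type 3 TZ"), then, after *or*, a type 2 TZ with the SCJ beyond the probe tip, and last, with no connective, "The lesion(s) cover > 75% of the cervix".
- **Referral sentence.** "If the above criteria for ablation are not met, the woman will be referred to a gynecologist at the closest facility".

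Three places say what is counted. Outcome measures names the number screened and the proportion of screen-positive women successfully treated. Sample size and power calculations uses same-day thermal ablation among HPV-positive women. The Treatment Rate in the Statistical analysis plan section counts thermal ablation or referral.

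**The concern.** A two-way clinical rule stated as two lists should sort every woman into one class. Here each list has its own connective, and lesion size appears in only one of them. A woman can satisfy every condition for ablation and still have a feature that the next paragraph names as a bar to it.

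Two things are at stake. The first is her management: two careful clinicians could read the same text and do different things. The second is measurement: the power calculation counts same-day ablation, so differences between sites or over time in reading the rule would show up as differences in the proportion treated.

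**Working it through.** The documents state no figure for this point. The check is one of logic, followed by an illustration of the effect on the numerator.

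**Inputs (VAT section).** Let S = suspected invasive or glandular disease.

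| Item | List | Condition |
|---|---|---|
| A | eligible | TZ fully visible, whole lesion visible, not into the endocervix |
| B | eligible | type 1 TZ |
| C | eligible | type 2 TZ, probe achieves complete ablation |
| D | not eligible | type 3 TZ |
| E | not eligible | type 2 TZ, SCJ out of reach |
| F | not eligible | lesion above 75% of the cervix |

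Eligible = not S and (A or B or C).

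**Profiles.** Combine S (yes/no), TZ type, SCJ within reach, extension into the endocervix, and lesion above 75%. Drop the impossible combinations: type 1 is always within reach with no extension, and type 3 is never within reach. For each value of S this leaves 2 (type 1) + 8 (type 2) + 4 (type 3) = 14, so 28 in all.

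**Three readings of the not-eligible list.**

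| Reading | Formula | On both lists | On neither list |
|---|---|---|---|
| Literal *and* | S and (D or E or F) | 0 | 9 |
| *And*, with F standing alone | (S and (D or E)) or F | 4 | 6 |
| *Or* throughout | S or D or E or F | 5 | 0 |

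No reading works. Under the literal one there is no overlap, but only because everyone on the second list already fails the first through S. Items D, E and F then do nothing, and a lesion above 75% without suspicion passes as eligible. Under the other two readings, where F or all of the items have effect, women appear on both lists.

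**Where the conflict lies.** Eight profiles meet the eligible list: 2 with type 1 TZ and 6 with type 2 TZ (all except those both out of reach and extending into the endocervix).

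- Group (i), lesion above 75%: 4 of the 8.
- Group (ii), visible type 2 TZ, no extension, SCJ out of reach: 2 of the 8, one of which is also in group (i).
- Together 4 + 2 − 1 = 5 of 8 carry a named not-eligible feature.

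These are counts of profiles, not of women.

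**Women on neither list.** Every such profile fails the eligible list, so the referral sentence covers it.

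**Effect on the numerator.** The plan takes 36% treated under standard of care and a 15-point gain, so 51%. It expects 98 HPV-positive women a month, hence 3 × 98 = 294 per quarter. With the arcsine formula, h = 2·arcsin√p₂ − 2·arcsin√p₁ and power = Φ(h·√(n/2) − 1.96). For 36% against 51% with n = 294 per group, power is 95.8%, in line with the plan's claim of at least 90% at 35% prevalence.

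Now assume that a share f of HPV-positive women counted as ablated within the 51% is referred instead:

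| Assumed f | Women of 2,940 | Same-day ablation | Quarterly power |
|---|---|---|---|
| 0 | 0 | 51% | 95.8% |
| 1% | about 29 | 50% | 93.1% |
| 2% | about 59 | 49% | 89.2% |
| 5% | 147 | 46% | 69.5% |

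The values of f are mine; the documents give none. Under the Treatment Rate, which counts referral, the numerator does not move at any f.

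**The case against.** The strongest reply is that the referral sentence settles matters: anyone who does not meet the criteria is referred. For women on neither list that is right. A reader might infer that a type 3 TZ without suspicion, or suspicion with a small lesion on a type 1 TZ, is left unclassified. Those women are referred, and the gap is only a drafting fault. The sentence does not help groups (i) and (ii), who do meet the eligible list. It also does not say whether the criteria it points back to include the second list.

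A reader might also infer from the stray *and* that a woman with suspected cancer could be ablated. The text does not allow this: every route to ablation requires the absence of suspicion.

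It can be said that the 75% item has no purpose under its heading except to exclude, so clinicians would read it that way. That is plausible, but it means overriding the literal *and*, and it leaves the eligible list contradicting the item. It is fair, too, that the affected group may be small, that about 6,900 of 8,400 women (82%) are expected at one hospital, and that cervical images are kept for quality control. These points limit the effect on the outcome without removing the contradiction.

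Finally, a reader might set the VAT wording against Table 1, "VIA and thermal ablation if eligible (Triage-and-treat", and conclude that the plan wavers between treating all eligible HPV-positive women and only those positive on VIA, so that the denominator is wrong or 51% is out of reach. Both texts make treatment depend on eligibility, the text shown nowhere says that HPV-positive, VIA-negative women go untreated, and Fig. 3 is not shown. A ceiling below 51% would need an assumed triage positivity for which the documents give no basis.

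**Conclusion.** The two lists contradict each other as written. The contradiction is confined to women without suspected invasive or glandular disease who meet an eligible item and have either a lesion above 75% of the cervix or a visible type 2 TZ with the SCJ out of probe reach.

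Group (ii) rests on taking the endocervix condition in the first eligible item to describe the lesion, which is the nearer noun. If it describes the TZ, group (ii) may fall away. Group (i) stands on either reading, for example with a type 1 TZ.

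The rule is applied to about 2,940 expected HPV-positive women, but the ambiguity touches only a subset whose size cannot be derived from the documents. Any reclassification moves the same-day ablation proportion one for one and leaves the Treatment Rate unchanged. Under Outcome measures the effect also depends on whether treatment completed after referral counts as success. The point therefore rests on the wording and on the management of these women; the power figures are illustration only.

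**What to change.** The investigators should reconcile the two lists in the protocol so that every examined woman falls in exactly one class. Four places need attention: the *and* that opens the not-eligible list, the *or* items of the eligible list, the standing of the 75% item (with no counterpart in the eligible list), and the out-of-reach item set against the first eligible item. The referral sentence should say which criteria it points back to, and Fig. 3 should be checked against the agreed text. The same wording should go on the case report form at all four sites. Which clinical rule is right is for the clinical lead, and none is proposed here.

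The cost is protocol and form wording plus a short note to sites. Sample size, design and analysis model do not change.
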